## Abstract

**Introduction:**

Delirium is a complex condition in which altered mental state and cognition causes severe distress and poor clinical outcomes for patients and families, anxiety and stress for the health professionals and support staff providing care, and higher care costs. Hospice patients are at high risk of developing delirium, but there is significant variation in care delivery. The primary objective of this study is to demonstrate the feasibility of an implementation strategy (designed to help deliver good practice delirium guidelines), participant recruitment and data collection.

**Methods and analysis:**

Three work packages in three hospices in the UK with public involvement in codesign, study management and stakeholder groups: (1) experience-based codesign to adapt an existing theoretically-informed implementation strategy (Creating Learning Environments for Compassionate Care (CLECC)) to implement delirium guidelines in hospices; (2) feasibility study to explore ability to collect demographic, diagnostic and delirium management data from clinical records (n=300), explanatory process data (number of staff engaged in CLECC activities and reasons for non-engagement) and cost data (staff and volunteer hours and pay-grades engaged in implementation activities) and (3) realist process evaluation to assess the acceptability and flexibility of the implementation strategy (preimplementation and postimplementation surveys with hospice staff and management, n=30 at each time point; interviews with hospice staff and management, n=15). Descriptive statistics, rapid thematic analysis and a realist logic of analysis will be used be used to analyse quantitative and qualitative data, as appropriate.

**Ethics and dissemination:**

Ethical approval obtained: Hull York Medical School Ethics Committee (Ref 21/23), Health Research Authority Research Ethics Committee Wales REC7 (Ref 21/WA/0180) and Health Research Authority Confidentiality Advisory Group (Ref 21/CAG/0071). Written informed consent will be obtained from interview participants. A results paper will be submitted to an open access peer-reviewed journal and a lay summary shared with study site staff and stakeholders.

**Trial registration number:**

ISRCTN55416525.

Strengths and limitations of this studyInnovative collaborative adaptation of a theoretically informed implementation strategy (Creating Learning Environments for Compassionate Care, CLECC) to deliver guideline-adherent delirium care in hospices (CLECC-Pal), including evaluation of feasibility and acceptability of an implementation strategy before testing at scale.Research waste minimised and patient/carer burden eliminated through use of existing patient outcome and process data.Involvement of public members since study inception and throughout study delivery and management.While the study hospices have diverse characteristics (locations, level of socioeconomic deprivation, forms of governance), they are all drawn from a single region of the UK.The sample size for surveys and interviews may limit the extent to which the complexity of staff and management characteristics, views and experiences can be explored.

## Introduction

Delirium is a complex condition characterised by fluctuating impairment of awareness, attention and cognition.^1^ Delirium causes severe distress for patients and families,^2^ anxiety and stress for the health professionals and support staff providing care,^3^ poor clinical outcomes^4 5^ and higher care costs (eg, longer inpatient stays).^6 7^ People nearing the end of life have a high risk of delirium,^2^ with risk factors such as medication, metabolic disturbance, pain, poor sleep, infection and dehydration acting cumulatively.^8^ Effective delirium care is driven by prevention where possible, timely detection and non-pharmacological management, with pharmacological interventions if appropriate.^9 10^ Hospices are an important but under-researched setting for the prevention and management of delirium.

An international systematic review reported that one-third of people in adult palliative care settings had delirium on admission, with two-thirds developing delirium during the admission.^8^ Across health services the health economic impact of delirium is significant. Although data are not available from palliative care settings, other estimates of health service costs from delirium show comparable costs to falls, diabetes and cardiovascular diseases.^11^

National Institute for Health and Care Excellence (NICE) Clinical Guideline 103^12^ and other international guidelines^13^ and standards,^14^ recommend strategies for delirium assessment, prevention and management. However, this is difficult in practice, with a disconnection between improved levels of delirium knowledge and the capacity of palliative care practitioners to implement changes. A recent international qualitative systematic review identified that practical and emotional support were needed to enable staff to assess, prevent and manage delirium.^15^

A recent survey of palliative care doctors (n=335) in the UK found that 38% never used delirium guidelines and that only 13% of palliative care teams used a tool (rather than clinical judgement) to assess for delirium at first inpatient assessment, with even fewer (9%) using a tool on an ongoing basis.^16^ Our survey of UK specialist palliative care units (n=220, mostly nurses)^17^ found that only 10% ever used a delirium screening tool, with only 5% following NICE guidelines by screening on admission, and only 6% screening daily thereafter. The importance of delirium care has been recognised in a national survey of dying patients, with 92% rating ‘being mentally aware’ as ‘very important’ and nearly as many (89%) citing ‘not being a burden on family’.^18^

Delirium detection, assessment, management and prevention is complex, depending on practical support (screening tools and clinical pathways) and communication^3 19^ between family and friends, volunteers, healthcare assistants, nurses allied health professionals (AHPs), social workers, doctors, hospice managers and board members. It also takes place at some of the most sensitive and emotionally fraught times in the lives of patients and their families. Therefore, guideline implementation requires a relevant and flexible strategy based on an understanding of how adaptation for different settings can be attained while retaining effectiveness.

To address this gap in knowledge about how to implement guideline-adherent delirium care, we shall first adapt an existing theoretically-informed implementation strategy that has been tested in acute hospital wards (Creating Learning Environments for Compassionate Care (CLECC)). CLECC has been found to foster and legitimise the reflection, learning, mutual support and innovation that can enable team members to progress from knowing to doing.^20^ It comprises a team study day, ward manager action learning sets, peer observations of practice, and involvement of all staff in mid-shift ‘cluster discussions’ and twice-weekly reflective discussions,^21^ and is shown mapped to the TIDieR checklist^22^ in table 1. We will then test the feasibility of a subsequent quasi-experimental study to evaluate the effect of the adapted CLECC (the intervention) on hospice staff delivery of guideline-adherent delirium care and subsequent improvement in patient outcomes (reduction in the number of delirium days, with a delirium day being one where the patient was classed as having delirium using Inouye *et al*’s chart-based instrument^23^).

**Table 1 T1:** CLECC^21^ components mapped using Template for Intervention Description and Replication (TIDieR) checklist^22^

Component	Why	What	Who	How	Where	When/How much	Tailoring and modifications	Fidelity
Study day	Prepare staff for the workplace elements of the intervention	Procedure: Introduction to CLECC Activities/discussion Questionnaires Film handouts	Appointed hospice lead clinician	Classroom based to include all hospice staff	Comfortable classroom that is geographically separate from the workplace	One day at beginning of implementation period, but may require more than one study day to ensure maximum attendance	Pending work package 1 codesign workshops	Attendance and feedback data from hospice lead clinician.
		Materials: PowerPoint presentation. Record of attendance. Summary of CLECC leaflet						
Action Learning sets	Real problems from own practice and devise action plan to address	Procedure: Session 1: relationships and rules Session 2: valuing staff Session 3: enhancing capacity CLECC Session 4: influencing seniors	Experienced facilitator and 4 to 8 leads of comparable position	Face to face at hospice site	At hospice site	4×4 hours action learning sets throughout intervention period	Pending work package 1 codesign workshops	Fidelity/ attendance
Peer review	Appreciate practice from observer perspective	Procedure: 2–3 × 1 hour observations Reflective summary Materials: Training video Poster of findings	2 team members nominate or nominated by lead and training given.	Outside of normal role to do this activity	At hospice site	Approximately 30 min training video prior to commencing 2–3 × 1 hour observations throughout implementation	Pending work package 1 codesign workshops	Fidelity
Mid-shift cluster discussions	Opportunities for feedback, group problem solving and support to individual team members.	Procedure: Mid-shift 5 min discussion	All team members on shift.	Mid-way through every shift.	At hospice site	5 min discussion mid-shift, initially instigated by lead but then to be maintained by staff	Pending work package 1 codesign workshops	Fidelity
Reflective discussions	To prompt personal reflections and narratives about individual experiences	Procedure: Scheduled meetings or drop in sessions with planned activities Materials: Devise a sustainability plan	All team members, including senior staff and temporary staff.	Can be scheduled time during shift or drop-in sessions.	At hospice site, in a comfortable room on or near place of care.	No of sessions dependent on the number of subjects needed to be discussed	Pending work package 1 codesign workshops	Fidelity

CLECC, Creating Learning Environments for Compassionate Care.

### Aims and objectives

This study will address key uncertainties about the implementation of guideline-adherent delirium care in hospices by demonstrating if it is possible to:

Coadapt an implementation strategy (CLECC) for use in hospices (work package 1, WP).Systematically and reliably collect data (including delirium diagnosis) from clinical records in a way that minimises burden for patients, families and staff (WP 2).Collect measures of staff engagement with the implementation strategy, delivery of guideline-adherent delirium care, and the costs of staff involvement (WP 2).Collect explanatory process data about staff use of the implementation strategy (WP 3).Estimate the number of hospice sites and in-patient episodes needed for the planned national quasi-experimental study.

WP 1 commenced June 2021, with WP 2 and 3 (and data collection) commencing August 2021. The study will be completed in February 2023.

## Methods and analysis

### Design summary

Table 2 presents the research questions and summarises the three WPs that will enable the above aims and objectives to be met. Figure 1 shows the study timeline and how the WPs are inter-related.

**Table 2 T2:** Overview of study design

Work package objective	Research question	Study type	Data collection	Timepoints
1. Refine CLECC-Pal implementation strategy	What are the core and adaptable components of an implementation strategy for guideline-adherent delirium care in hospices?	Experience-based codesign	Workshops	Before and during implementation
2. Demonstrate feasibility of future quasi-experimental study	Is it feasible to collect sufficient outcome data (both implementation and clinical), explanatory process data, and cost data in a future effectiveness evaluative study in palliative care settings?	Feasibility study	Patient demographics and delirium diagnosis and management (clinical records) No of staff engaged in CLECC-Pal	Baseline and follow-up During implementation and follow-up
3. Assess acceptability and flexibility of CLECC-Pal implementation strategy	How can a codesigned implementation strategy for guideline-adherent delirium care be operationalised with fidelity to function in different hospice inpatient settings?	Realist process evaluation	Survey Fidelity to CLECC-Pal Interviews	Baseline and follow-up Start, middle and end of 3-month period using CLECC-Pal Follow-up

CLECC, Creating Learning Environments for Compassionate Care.

**Figure 1 F1:**
[figure not shown]
Study flow chart and timeline summary. WP, work package.

### Settings

Three adult hospices in northern England (UK). Two hospices in this study are located in socio-economically deprived urban areas (one with a significant minority ethnic group population) and one hospice in an affluent rural/urban area. One hospice is run by a national charity, with the other two hospices run by independent charities.

### Patient and public involvement

This study supports the involvement of patient and public involvement (PPI) in accordance with the framework for good public involvement as detailed by the UK standards for public involvement.^24^ Public involvement group members contributed to study design, with one member joining the monthly Study Management Group meetings, cofacilitating workshops (WP 1) and a further member Chairing the Study Steering Committee. The study’s public involvement group will meet three to four times over the duration of the study to discuss public involvement challenges in the research, the implications of emerging study findings, and the development of public-facing research outputs and the next steps in the research cycle.

### WP1: adaptation (codesign) of CLECC for guideline-adherent delirium care

An experience-based codesign group^25–27^ of people with lived experience of delirium (themselves or in a family member or friend), staff and management from across the study sites and the region will meet for online workshops (maximum 3 hours duration) at months 2, 8 and 14 to adapt the CLECC strategy for use in hospices (see figure 1). The first of these codesign workshops will be held separately for public and staff to facilitate reflection within a broader public or staff ‘group’ and to underpin interactions between public and staff at subsequent joint workshops. The interactions in these joint codesign workshops are considered essential for participants to share their experiences, develop an appreciation of others’ experiences, and open up new ways of thinking about how to meet challenges that will directly inform codesign.^28^ Consistent with the INVOLVE principles for coproducing research,^29^ workshops will be codeveloped with our public involvement group and cofacilitated by an experienced Public Involvement group member.

Potential public participants will be invited through existing national PPI networks to join the codesign workshops. Potential hospice staff and management participants (clinicians, volunteers, managers and board members) will be invited through existing communication channels at each site and in consultation with managers. Information will be provided for potential participants with an opportunity to discuss in more detail prior to taking part. Workshops will be scheduled to fit with existing commitments and day-to-day practice at each hospice. PPI team member (MO) will provide input into all aspects of invitations, information provision and workshop design.

We shall endeavour to maximise diversity within the workshops but acknowledge the tension between attaining diversity across every potential aspect and a maximum workable number of workshop participants of around 15. We shall keep this under review with PPI team member MO.

Central to the conduct of the workshops will be the use of ‘touch points’ to communicate other peoples’ experiences and provide a focus to spark discussion and exploration from different perspectives.^26^ Touch points are the events which significantly shape people’s positive or negative experience of an event or service. It could be the sharing of a personal or professional experience of delirium care by a workshop participant, or a short film or news item about palliative care services generally or delirium specifically. These will be used to trigger discussion about the detection, assessment, prevention and management of delirium, how CLECC can be adapted for hospices and support implementation of delirium guidelines.

Table 3 provides an overview of the schedule and content of the codesign workshops.

**Table 3 T3:** Codesign workshops schedule and content

Workshop focus	Participants	When, duration	Content
1a. Introduction and initial refinement of CLECC-Pal	Public members	Month 2, 2 hours	Introductions Discussion about the principles of equitable participation Discussion about the codesign approach to workshops Introduction to the CLECC strategy and exploration of priority aspects for adaptation Identification of individual working groups’ role in exploring and refining site-specific or issue-specific aspects of the CLECC strategy before Workshop 2 Agreement on feedback processes outside of the workshops and focus of agenda for Workshop 2
1b. Introduction and initial refinement of CLECC-Pal	Hospice staff and volunteers	Month 2, 2 hours	As for Workshop 1a
2. Refinement of CLECC-Pal	Public members, hospice staff and volunteers	Month 8, 3 hours	Feedback from individual working groups Discussion of emerging findings from work package 3 (realist process evaluation) Specification of suggested adaptations to CLECC Identification of further individual working groups to refine site- or issue-specific aspects of the CLECC strategy Agreement on focus of agenda for Workshop 3
3. Final specification of CLECC-Pal and celebration	Public members, hospice staff and volunteers	Month 14, 3 hours	Feedback from individual working groups Discussion of further findings from work package 3 (realist process evaluation) Final specification of adaptations to CLECC Celebration of codesign outputs

CLECC, Creating Learning Environments for Compassionate Care.

### WP 2: feasibility study

Feasibility will be assessed in the following key areas:

Patients:Ability to collect high quality, anonymised delirium outcome and process (extent of guideline-adherent care) data from clinical records.Variability of baseline delirium day measurement to calculate the sample size for a subsequent national study.Staff and volunteers: Number of relevant hospice staff and volunteers’ participation in CLECC-Pal activities (proportion of relevant staff engaging and maintaining engagement).Economic: Ability to collect cost data in relation to CLECC-Pal staff activities.

The codesigned CLECC-Pal (for initial version, see table 1) will be introduced to clinical and support staff, volunteers and managers at each hospice in a study day that will include training in guideline-recommended delirium care. The study team will support the identified clinical lead to introduce and use CLECC-Pal, including action learning sets, mid-shift ‘cluster discussions’, twice-weekly reflective discussions and peer observations of practice, over a minimum 12-week period. The study day ethos will emphasise how hospices should take ownership of using CLECC-Pal with only modest support from the study team.

### Data collection and analysis

#### Patients

Baseline and follow-up (pre and post) clinical record data will be collected. Data will be collected through remote access to the clinical record where electronic records allow, or from the paper record. At each of the three hospices, case note collection (total n=300) will comprise:

Baseline (pre): 50 consecutive patients who completed their in-patient stay immediately prior to the start of the hospice using CLECC-Pal.Follow-up (post): 50 consecutive patients completing their in-patient stay from week 4 of starting use of CLECC-Pal.

Clinical record data collected by the researcher will be anonymised at the point of extraction and include:

Demographic data (baseline only): age, sex, main medical condition, ethnicity, postal code (converted to Index of Multiple Deprivation (IMD) score).Delirium diagnosis using the Inouye *et al* case note tool.^23^Delirium management: including evidence of use of delirium screening tools, risk assessments and individualised delirium management care plans.

Clinical record data will be extracted using an expanded version of the prospectively validated (74% sensitivity, 83% specificity) chart-based instrument developed by Inouye *et al* for detecting potential delirium diagnoses from clinical records.^23^ The instrument (data extraction proforma, see online supplemental file 1) will enable us to assess whether case-note recorded symptoms of delirium (and therefore number of patient days with delirium) can be linked to time points during the person’s admission when actions around delirium assessment, management and prevention (consistent with guidelines) did or did not take place. Our ‘expanded’ version of the instrument will include questions about other actions to support delirium assessment, management and prevention that may be recorded in the notes, as shown in table 4. We shall report the percentage of clinical records where information about each of these actions is recorded. Where a person experiences multiple episodes of delirium within one admission, each episode will be recorded separately and linked through the anonymised case number.

10.1136/bmjopen-2021-060450.supp1Supplementary data

**Table 4 T4:** Additional delirium assessment items to be derived from clinical records and means of assessing feasibility of data collection

Delirium-related action	Assessment of feasibility
Use of richmond agitation-sedation scale and 4AT screening tools	% completed % reassessments completed at appropriate timepoints
Medication reviews (to minimise deliriogenic medication)	% completed % reassessments completed at appropriate timepoints
Diagnostic and Statistical Manual of Mental Disorders (DSM-V) delirium assessment	% completed % reassessments completed at appropriate timepoints
Degree of sedation or agitation	% completed
Individualised delirium care plans	% completed % reviewed at appropriate timepoints
Presence/absence of delirium	% documenting start and end of delirium episode(s) % documenting delirium-free days

Where judgements about what to record on the pro-forma need to be made, justification for these will be recorded on the form. Any uncertainty about how the information in the case notes should be recorded on the proforma will be discussed with a second clinician (CJ) and justification for the final decision recorded.

The number of patient records from which it was possible to extract clinical record data longitudinally over the duration of their inpatient admission will be reported both as a simple count and as a percentage of the total number of in-patients with a diagnosis of delirium in each hospice each month.

Sample size: Based on our pilot work in one hospice (comparable in size to the hospices in this study) which identified a monthly occurrence of 32 inpatient episodes of delirium, retrospectively collecting clinical record data for all patients whose episode of in-patient care is completed (up to a maximum of 50 per hospice) will provide us with enough data to answer feasibility questions about data quality and enable us to capture frequent events regarding care planning. We do not propose to investigate less-frequent events such as antipsychotic use.

Analysis: Baseline demographic and clinical characteristics of the study population (age, sex, primary medical condition, ethnicity, postal code (to derive IMD)) will be presented using descriptive statistics. Mean (SD) will be reported for continuous data and raw count (number, percentage) will be reported for nominal data. The variation around baseline delirium days will be calculated to inform the sample size and number of hospices needed for the subsequent national study.

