#### Staff and volunteers

In consultation with operational and clinical management at each site, a hospice study lead has been identified through whom the following denominators will be established:

Number of staff working on or rotating through the in-patient unit of the hospice.Number of volunteers active within the in-patient unit of the hospice.Total number of documented in-patient delirium episodes or (if total number cannot be established) number of patients with at least one case-note diagnosis of delirium per in-patient admission in the hospice.

Level of staff engagement with CLECC-Pal during the implementation period will be assessed weekly by the hospice study lead completing a rapid report of numbers of:

Staff indirectly involved in delivering delirium care who attend the team study day, action learning sets, feedback following peer observations of practice, mid-shift cluster discussions, and reflective discussions.Staff and volunteers who do not engage with CLECC-Pal.Staff and volunteers who decrease or stop their engagement with CLECC-Pal.Peer observations of practice achieved.People approached, reported by professional group and role, who agree to participate in using CLECC-Pal.

The rapid report will also record reasons for:

Staff and volunteers’ non-engagement or dropout.Modifications made in the use of CLECC-Pal.

Quantitative data will be analysed descriptively using radar plots. Qualitative data will be rapidly analysed deductively using a Framework approach.^30^ Analyses will inform more detailed exploration in interviews (WP3) and will be shared with participating hospices to inform their ongoing use of CLECC-Pal.

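### The record-extraction percentage divides records from all consecutive stays by in-patients diagnosed with delirium, so it can exceed 100% and does not measure completeness; a staff-attendance line also needs a wording correction

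*Protocol article*

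**What the plan says.** **Record extraction (WP 2, Patients).** The sample is introduced as "At each of the three hospices, case note collection (total n=300) will comprise" two sets. The baseline set is "50 consecutive patients who completed their in-patient stay immediately prior to the start of the hospice using CLECC-Pal" and the follow-up set is "50 consecutive patients completing their in-patient stay from week 4 of starting use of CLECC-Pal". Neither is restricted to patients with delirium. The sample-size paragraph describes the same frame: every completed stay, up to 50 per hospice. The number of records that could be followed through the whole admission is to be given as a plain count and also "as a percentage of the total number of in-patients with a diagnosis of delirium in each hospice each month".

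**Staff attendance (WP 2, Staff and volunteers).** The first denominator is "Number of staff working on or rotating through the in-patient unit of the hospice", and a second covers volunteers active on the unit. The weekly rapid report's only line on attendance begins "Staff indirectly involved in delivering delirium care who attend the team study day" and goes on to the other CLECC-Pal activities.

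**The concern.** A feasibility percentage should answer this question: of the records we set out to use, how many could we use? Here the top of the fraction counts records from all kinds of stay, and the bottom counts only patients with a delirium diagnosis, by month. The result is not a proportion. The figure above 100% is odd but visible. The less visible problem is that a value near 100% can arise when about half the records were unusable, so poor extraction could be read as complete. Collecting data from clinical records is one of the stated feasibility objectives, so the figure should mean what it appears to mean.

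The attendance line has a related fault on a smaller scale. As worded it leaves out staff who give direct care, and volunteers, although both belong to the stated denominators.

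**Working it through.** **Inputs from the protocol article**
- Sample: 3 hospices, 2 periods, 50 stays each (WP 2, Patients).
- Annual admissions 192 to 384 per hospice, delirium incidence 40% to 60% (Discussion).
- Pilot: 32 delirium episodes a month in one hospice of comparable size (WP 2, sample size).

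**Reproducing the plan's figure.** 3 × 2 × 50 = 300, which agrees with the stated total. The numerator is therefore drawn from 50 unrestricted stays per hospice per period.

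**Matched period.** Suppose the denominator covers exactly the period of the 50 stays and the Discussion's incidence applies to them.
- Delirium patients: 50 × 0.40 = 20 to 50 × 0.60 = 30.
- All 50 records extractable: 50/30 = 167% to 50/20 = 250%.
- Records needed to show 100%: 20 to 30 of 50, that is 40% to 60% extractable.

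**Period as written (per month).**
- Admissions per month: 192/12 = 16 to 384/12 = 32.
- Time to accrue 50 stays: 50/32 = 1.6 months to 50/16 = 3.1 months, so the sample covers some months only in part.
- Delirium patients per month: 16 × 0.40 = 6.4 to 32 × 0.60 = 19.2.
- A full set of 50 over one month's delirium patients: 50/19.2 = 260% to 50/6.4 = 781%.

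**Patients or episodes.** The pilot's 32 episodes a month compare with an implied 6.4 to 19.2 patients a month, a ratio of 32/19.2 = 1.7 to 32/6.4 = 5.0. Repeat episodes within an admission could explain part of the gap. Any delirium-based denominator therefore has to state its unit.

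**With the sampled stays as denominator.** Complete extraction gives 50/50 = 100%, and the figure cannot exceed that.

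**Staff attendance.** If a share s of unit staff give direct care, the line as worded cannot exceed 1 − s even when everyone attends. The documents give no value for s, so no size can be put on this.

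**The case against.** **The extraction figure decides nothing.** The progression thresholds in the Discussion concern use of CLECC-Pal (fidelity to core components) and 4AT screening. Data quality is mainly answered by the Table 4 items, which are percentages of clinical records, a sound denominator. The simple count is reported too, so a reader can form the fraction of 50. All of this stands, and it limits the importance of the point. It does not make the stated percentage right.

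**The numerator may be meant as delirium patients only.** The text does not say so, and the sampling frame is all completed stays. That reading would also still set a capped consecutive sample against calendar months it only partly covers.

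**The staff wording is probably a slip.** The WP 3 Surveys section has the mirror image: after naming staff in direct care it adds a second group as directly involved, where indirectly must be meant. The same rapid report counts non-engagers, people who reduce or stop, and people agreeing to take part by professional group and role. Table 1 provides for attendance records at the study day and action learning sets, and the Economic section records staff and volunteer hours. A reader might infer that direct-care staff are never counted as engaging. The documents do not support that, because these items partly recover their engagement.

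**Two further inferences go beyond the text.** A reader might conclude that the extraction percentage would fall as CLECC-Pal improves detection. That requires diagnosis to mean one documented by clinicians, whereas the Patients section lists a diagnosis made with the chart-based tool. A reader might also conclude that hospices would mix units, because the Staff and volunteers section allows a fallback from episodes to "number of patients with at least one case-note diagnosis of delirium per in-patient admission in the hospice". Nothing states that this list feeds the extraction percentage, which is worded in in-patients.

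**Conclusion.** The extraction percentage is wrongly defined: its numerator is not contained in its denominator and the two cover different periods. Complete extraction would read as about 167% to 250% over a matched period, and 100% would not mean complete extraction. This range assumes that the Discussion's 40% to 60% incidence applies to the sampled stays and that diagnosed patients match that incidence. The mismatch itself needs no assumption.

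The attendance line is a secondary, minor point: a probable one-word error whose effect cannot be sized from the documents.

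A reader might take these as headline results that threaten the go/no-go decision. Neither percentage is named as a progression criterion, and no sample size or progression rule changes. This is a worthwhile correction to descriptive feasibility measures, not a must-fix.

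**What to change.** **Extraction percentage.** Use as denominator the consecutive completed stays sampled in that hospice and period (50). This is one sentence and needs no new data.

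**Optional delirium-only figure.** If one is wanted, restrict numerator and denominator to the same patients and the same period, and count patients, not episodes. Identify delirium in a way that does not depend on the record being extractable. If delirium status comes from the extraction itself, an unusable record cannot be classified, drops out of both counts, and pushes the figure towards 100%. An independent identification would have to be made stay by stay, which may be extra work for the hospices. If that is not available, leave the figure out.

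**Attendance line.** Reword it to cover *staff and volunteers directly or indirectly involved*, with staff and volunteers counted separately so that each matches its stated denominator. This changes one line on the rapid-report form. The form is completed weekly, so an early change loses least.
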